## Abstract

**Background:**

Upper limb motor recovery is one of the important goals of stroke rehabilitation. Intermittent theta burst stimulation (iTBS), a new type of repetitive transcranial magnetic stimulation (rTMS), is considered a potential therapy. However, there is still no consensus on the efficacy of iTBS for upper limb motor dysfunction after stroke. Stimulus dose may be an important factor affecting the efficacy of iTBS. Therefore, we aim to investigate and compare the effects and neural mechanisms of three doses of iTBS on upper limb motor recovery in stroke patients, and our hypothesis is that the higher the dose of iTBS, the greater the improvement in upper limb motor function.

**Methods:**

This prospective, randomized, controlled trial will recruit 56 stroke patients with upper limb motor dysfunction. All participants will be randomized in a 1:1:1:1 ratio to receive 21 sessions of 600 pulses active iTBS, 1,200 pulses active iTBS, 1,800 pulses active iTBS, or 1,800 pulses sham iTBS in addition to conventional rehabilitation training. The primary outcome is the Fugl-Meyer Assessment of the Upper Extremity (FMA-UE) score from baseline to end of intervention, and the secondary outcomes are the Wolf Motor Function Test (WMFT), Grip Strength (GS), Modified Barthel Index (MBI), and Stroke Impact Scale (SIS). The FMA-UE, MBI, and SIS are assessed pre-treatment, post-treatment, and at the 3-weeks follow-up. The WMFT, GS, and resting-state functional magnetic resonance imaging (rs-fMRI) data will be obtained pre- and post-treatment.

**Discussion:**

The iTBS intervention in this study protocol is expected to be a potential method to promote upper limb motor recovery after stroke, and the results may provide supportive evidence for the optimal dose of iTBS intervention.

## Introduction

1.

Motor dysfunction of the upper limb occurs in 73–88% of first-ever stroke survivors, and 55–75% of patients suffer residual motor dysfunction of the upper limb 3 to 6 months after stroke onset (Lawrence et al., 2001). Stroke patients with upper limb motor dysfunction often have limited independence in daily activities and reduced quality of life (Faria-Fortini et al., 2011). Therefore, improving upper limb function is an important goal of stroke rehabilitation (Pollock et al., 2014; Veerbeek et al., 2017). To date, conventional rehabilitation training remains the primary treatment for upper limb motor dysfunction after stroke, but effectiveness is limited. It is necessary to develop other therapeutic methods to improve the effectiveness of conventional rehabilitation training for upper limb motor dysfunction after stroke (Barreca et al., 2003; Coscia et al., 2019).

In recent years, repetitive transcranial magnetic stimulation (rTMS) has been increasingly used as a safe and non-invasive neuromodulation technique for functional rehabilitation of the upper limb after stroke (Du et al., 2016; Kim et al., 2020; Ni et al., 2022; Ahmed et al., 2023). rTMS plays a therapeutic role by penetrating the skull through the magnetic field generated by the coil transient current to generate an induced current to stimulate neurons, thereby regulating cortical excitability and modulating neuroplasticity (Du et al., 2019; Brown et al., 2021; Bai et al., 2022). First applied to healthy subjects by Huang et al. (2005), theta burst stimulation (TBS) is a novel type of rTMS that can achieve similar or better results than conventional rTMS in a shorter stimulation session (Di Lazzaro et al., 2011; Blumberger et al., 2018; Si et al., 2019). Moreover, the stimulation intensity of TBS is lower, reducing the risk of adverse effects, especially seizures (Gutiérrez-Muto et al., 2020). Excitatory or inhibitory effects can be achieved by adjusting the stimulation time and interval, whereas intermittent theta burst stimulation (iTBS) has excitatory effects on the cerebral cortex (Ogata et al., 2021; Bai et al., 2023). In the iTBS, a 2 s train of TBS is repeated every 10 s for a total of 190 s (600 pulses) (Huang et al., 2005). Currently, the main target of stimulation is the primary motor cortex (M1) over the ipsilateral hemisphere when iTBS is used to treat poststroke upper limb motor dysfunction (Gao et al., 2022; Huang et al., 2022; Tang et al., 2022). Although iTBS appears to be a promising treatment for upper limb motor recovery in stroke patients, it is noteworthy that the evidence for beneficial effects of iTBS on post-stroke upper limb motor dysfunction is inconclusive. Some clinical trials have been conducted to explore the effects of iTBS on upper limb motor recovery after stroke, but the results were controversial (Talelli et al., 2012; Khan et al., 2019; Liu et al., 2019). Thus, improving the effectiveness of iTBS has become the focus of research.

One of the most important factors influencing the effectiveness of iTBS is the stimulus dose (Volz et al., 2013; Chung et al., 2016). When studying stroke patients, most researcher used a block of 600 iTBS pulses (Ackerley et al., 2014, 2016; Watanabe et al., 2018; Chen et al., 2019; Ding et al., 2021) and a few used two blocks of 600 pulses iTBS (Hsu et al., 2013; Chen et al., 2021). Previous studies in healthy human subjects suggested that iTBS might dose-dependently modulate neural plasticity, i.e., the higher the dose of iTBS, the greater the changes in neural plasticity induced (Nettekoven et al., 2014; Yu et al., 2020). Nettekoven et al. (2014) applied three blocks of 600 pulses iTBS to motor cortex and found that the cortical excitability enhancement effect was significantly greater than two blocks of 600 pulses iTBS and one block of 600 pulses iTBS. They also found that functional connectivity between M1 and ipsilateral dorsal premotor cortex continued to increase in a dose-dependent manner after 1,800 pulses of iTBS over M1. However, studies in healthy human subjects are insufficient to support the clinical application of iTBS. Other studies revealed that in patients with neurological disorders, high doses of rTMS produced stronger and longer lasting therapeutic responses than low doses (Nyffeler et al., 2009; Williams et al., 2018), but an agreement on how to select the best dose of iTBS for stroke patients with upper limb motor dysfunction is limited until now. There is a lack of studies comparing the difference in efficacy of different doses of iTBS for upper limb motor dysfunction in stroke patients.

Therefore, the objectives of this randomized controlled clinical trial are: (1) to investigate the safety and efficacy of one block of iTBS (600 pulses-iTBS), two blocks of iTBS (1,200 pulses-iTBS), or three blocks of iTBS (1,800 pulses-iTBS) in the treatment of upper limb motor dysfunction in stroke patients; (2) to compare the efficacy of three doses of iTBS; (3) to explore the neural mechanism of upper limb motor recovery after stroke using resting-state functional magnetic resonance imaging (rs-fMRI). Our hypothesis is that the higher the dose of iTBS, the greater the improvement in upper limb motor function in stroke patients. This study may provide new insights into the efficacy and underlying neuroplastic mechanisms of iTBS for treating poststroke upper limb motor dysfunction.

## Methods

2.

### Study design

2.1.

This is a prospective, single-center, randomized, parallel, sham-controlled clinical trial. This study will be conducted at Beijing Bo’ai Hospital, China Rehabilitation Research Center (Beijing, China). Hospitalized patients will be screened in accordance with strict inclusion and exclusion criteria. After written informed consent is obtained, demographic information collection and baseline assessments are scheduled for each patient. All participants will be randomly assigned with a ratio of 1:1:1:1 to one of the following four groups: Group A, Group B, Group C, and Group D. Details of the study design and data collection are presented in Figure 1 and Table 1. Behavioral assessments will be performed at baseline (T0), at the end of the iTBS intervention (T1), and 3 weeks post-treatment (T2) to assess upper limb motor function, activities of daily living (ADLs) performance, and quality of life. In addition, rs-fMRI data will be collected before and after the end of the intervention. This study has been approved by the Medical Ethics Committee of China Rehabilitation Research Center (No.: 2022-149-01) and registered on www.chictr.org.cn under the registration number ChiCTR2300068177.

**Figure 1 fig1:**
[figure not shown]
Study flow diagram. a, FMA-UE; b: WMFT; c, GS; d, MBI; e, SIS; f, MRI. iTBS, intermittent theta burst stimulation. T0, pre-treatment; T1, post-treatment; T2, at the 3-weeks follow-up.

**Table 1 tab1:** Overview of data collection and study timings.

Study period	Pre-enrollment (−7 d)	T0 (−3 to 0 d)	Intervention (0–21 d)	T1 (21 + 3 d)	T2 (42 ± 3 d)
Screening	×				
Enrollment	×				
Informed consent	×				
Random allocation		×			
Demographic information		×			
FMA-UE		×		×	×
WMFT		×		×	
GS		×		×	
MAS	×	×		×	
MBI		×		×	×
SIS		×		×	×
MRI		×		×	×
Adverse event		×	×	×	×

### Participants

2.2.

#### Inclusion criteria

2.2.1.

Participants are considered eligible if they meet the following criteria: (1) have a unilateral ischemic or hemorrhagic subcortical stroke; (2) first or previous stroke without residual disability (modified Rankin Scale ≤1 before this onset); (3) 1–6 months post-stroke; (4) are 35–75 years old; (5) presented with a unilateral upper limb motor dysfunction with a Brunnstrom stage score between 2 and 5 in the upper limb or hand; (6) can sign an informed consent form.

#### Exclusion criteria

2.2.2.

Participants will be excluded from the study if they meet the following criteria: (1) have a neurological impairment, upper limb limitation, amputation, joint swelling, contracture, severe pain, or other hand condition caused by a subtentorial stroke, brain tumor, brain trauma, fracture, or other disease; (2) the modified Ashworth scores (MAS) for the shoulder, elbow, wrist, and fingers of the affected upper extremity are all in the 3–4 range; (3) contraindications involving rTMS and rs-fMRI (e.g., skin damage at the stimulation site, claustrophobia, epilepsy history, intracranial implant, cardiac pacemaker); (4) have a disturbance of consciousness (National Institute of Health stroke scale (NIHSS) 1(a) ≥1); (5) have a malignant hypertension; (6) have a malignant tumor or any cause other than a stroke that results in a life expectancy of less than 1 year; (7) have severe aphasia (NIHSS language item ≥2), dysarthria (NIHSS dysarthria item ≥2), cognitive impairment (Mini-mental State Examination (MMSE) score ≤20), deafness, etc., such that they are unable to communicate, understand or follow instructions, and cannot cooperate with treatment and assessment; (8) have a major depressive disorder or anxiety disorder (Hamilton Depression Scale (HAMD)-17 score ≥18; Hamilton Anxiety Scale (HAMA)-score ≥21) or have been diagnosed with another mental disorder; (9) medication of antidepressants or benzodiazepines; (10) have severe sensory impairment (NIHSS sensory items = 2) or severe neglect (NIHSS neglect items = 2); (11) received neuromodulation therapy such as rTMS, transcranial electrical stimulation, and transcranial focused ultrasound within 3 months prior to enrollment; (12) have a history of alcohol or drug abuse; (13) are ineligible for participation in this trial due to other examination abnormalities; (14) are pregnant, or plan to get pregnant; (15) are participating in other clinical trials.

#### Withdrawal criteria

2.2.3.

Participants will be asked to withdraw from this trial if they meet the following criteria: (1) other neuromodulation therapies similar to iTBS are added during the study period; (2) miss iTBS treatment for 3 or more consecutive days or not complete treatment within 26 days; (3) have a sudden worsening of a stroke or other serious medical condition during the study period; (4) refuse to continue treatment; (5) the iTBS protocol is arbitrarily changed; (6) lost visits.

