### Sample size

2.3.

According to a previously published meta-analysis comparing iTBS and sham stimulation (Zhang et al., 2017), the expected effect size Cohen’s d for the comparison of the two groups was 0.6, and the effect size (f) for the comparison of the corresponding four groups was approximately 0.3. Using G*Power v3.1.9.2, the estimated sample size required for a 4-group design with a ratio of 1:1:1:1, given a power of 0.95 and a 2-tailed alpha error probability of 0.05, is 44 patients in total. Considering a dropout rate of 20%, at least 14 participants are needed for each group. Therefore, 56 patients will be enrolled in this study.

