### Outcome measures

2.6.

The Fugl-Meyer Assessment of the Upper Extremity (FMA-UE) score from baseline (T0) to end of intervention (T1) is defined as the primary outcome. The FMA-UE is a standardized scale of upper limb motor impairment ranging from 0 to a maximum of 66 points (Fugl-Meyer et al., 1975; Chen Y. F. et al., 2022). Secondary outcomes are the Wolf Motor Function Test (WMFT), Grip Strength (GS), MAS, Modified Barthel Index (MBI), and Stroke Impact Scale (SIS). The WMFT consists of 15 tasks, each of which must be completed in at least 120 s, and the performance on each task is scored on a six-point scale (0–5) (Morris et al., 2001; Wolf et al., 2001). The GS is measured with a grip dynamometer. During the measurement, the patient’s shoulder joint is abducted to 90°, the elbow joint is flexed to 90°, and the forearm is placed on the table. The patient is instructed to hold the grip dynamometer as hard as possible (Bertrand et al., 2015). The grip dynamometer automatically records the highest value. A total of 3 measurements are taken with a 1-min rest interval between each measurement. The MAS is commonly used to assess spasticity. The MAS scores for the shoulder, elbow, wrist, and fingers of the affected upper extremity will be recorded. The MBI is used to assess the patient’s ability to perform activities of daily living (ADL), including 10 items out of 100 points (Ohura et al., 2017). The SIS is one of the commonly used scales to evaluate the quality of life of stroke patients, which consists of eight items, and each item has a full score of 100 points (Mulder and Nijland, 2016), and we will take the average score of the eight items as the outcome. Each participant will undergo the following clinical assessments pre-treatment (T0), post-treatment (T1), and at the 3-weeks follow-up (T2): FMA-UE, MBI, SIS. The following clinical assessments will be performed only before and after treatment: WMFT, GS, MAS. We will also perform exploratory analyses based on the rs-fMRI data collected before and after the treatment.

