### Data analysis

2.7.

We will use SPSS version 25 for statistical analysis. Analysis of variance (continuous and ordinal data) or χ^2^ tests (categorical data) will be used to compare demographic and baseline characteristics. A mixed-design ANOVA (between-subjects factor: group; within-subjects factor: time; and time-by-group interaction) will be used to detect any significant differences in the change of outcomes. Any factor with a significant difference between the groups at the baseline will be included as a covariate in the ANOVAs. If a significant time-by-group interaction effect is found, comparisons using pairwise *t*-tests will be performed by separately comparing the changes from baseline. Bonferroni correction is applied for *post hoc* tests. Before entering the data into the ANOVAs, the Shapiro–Wilk test will be used to test whether the data are normally distributed. For non-normally distributed measures, the non-parametric Kruskal-Wallis H test is performed to compare across conditions. The level of significance is defined as *p* < 0.05 (2-tailed). For missing data, intention-to-treat (ITT) analysis is used (Matilde Sanchez and Chen, 2006).

The pre-processing of the MRI data will be in accordance with the previously described pipeline (Yeo et al., 2011). After preprocessing, regional homogeneity (ReHo), degree centrality (DC), amplitude of low frequency fluctuations (ALFF), and seed-to-voxel analyses will be performed to measure functional connectivity within motor networks. ReHo is calculated based on the Kendall’s concordance coefficient, which is used to measure the time-series synchronization between a given voxel and neighboring voxels, with higher values representing better concordance between the local voxel and the regional brain activities. In network analysis, DC is the most direct measure of node centrality. A higher degree of a node means that the node has a higher DC and the node is more important in the network. The ALFF value is related to the strength of local neural activity. It is often used to measure the BOLD signal in the frequency range of 0.01–0.1 Hz (Zang et al., 2004). Differences between conditions are considered significant if *p* < 0.05 at the voxel level. A false discovery rate (FDR) cluster corrected *p* < 0.05 is applied.

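### Withdrawal for adherence or clinical events is from the whole trial, with no outcome follow-up provided for, which conflicts with the intention-to-treat statement offered as the missing-data method

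*Protocol article*

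**What the plan says.** The Withdrawal criteria section opens: "Participants will be asked to withdraw from this trial if they meet the following criteria". What is ended is participation in the trial, not the stimulation alone. One criterion concerns adherence: "miss iTBS treatment for 3 or more consecutive days or not complete treatment within 26 days". Others are added neuromodulation, sudden worsening of the stroke or another serious condition, and: "refuse to continue treatment; (5) the iTBS protocol is arbitrarily changed; (6) lost visits".

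The schedule in Table 1 and the Outcome measures section place FMA-UE at T0, T1 and T2. Neither they nor any other section says whether someone who has met a withdrawal criterion is still assessed at T1 or T2.

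The Data analysis section gives one sentence on missing values: "For missing data, intention-to-treat (ITT) analysis is used", with a citation. The model is described thus: "A mixed-design ANOVA (between-subjects factor: group; within-subjects factor: time; and time-by-group interaction) will be used". On software it says: "We will use SPSS version 25 for statistical analysis". It names neither the SPSS procedure nor the visits that make up the time factor. The primary outcome is the FMA-UE "score from baseline (T0) to end of intervention (T1) is defined as the primary outcome".

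**The concern.** Two different things are merged. Stopping study treatment is a matter of patient care and adherence. Leaving the trial is a matter of data collection. When the first triggers the second, the primary outcome is lost for people who could still have attended the T1 visit.

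The events concerned arise after randomisation and may be related both to the assigned dose and to recovery. Worsening and refusal of treatment are the clearest cases. The trial's hypothesis is a gradient across doses, so losing such people unevenly across the four groups could create or hide part of that gradient. Randomisation would no longer protect the comparison.

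Naming intention-to-treat as the answer to missing data does not repair this. It is a rule on inclusion and grouping, and it says nothing about which value stands in for an outcome that was not measured.

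**Working it through.** **1. The two sections side by side**

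- Withdrawal criteria: participants who meet an adherence or clinical threshold are asked to leave the trial.
- Data analysis: missing data are handled by intention-to-treat, that is, all randomised participants are analysed as assigned.
- Followed literally, the first removes the T1 and T2 outcomes of people whom the second promises to analyse. No third statement connects them, either by continued assessment or by a method that supplies or models the missing values.

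**2. What the named model does with incomplete cases**

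- A mixed-design ANOVA run in the standard SPSS repeated-measures procedure drops any case with a missing visit. Without imputation, the analysed set is then the completers of the visits entered.
- With T0 and T1 only, a missing T2 removes nobody.
- With T0, T1 and T2, a participant who has the full primary outcome but no T2 is also dropped.

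The article does not say which applies. The sample size offers a hint. Inputs from the Sample size section are four groups, alpha 0.05, power 0.95 and this effect size: "the effect size (f) for the comparison of the corresponding four groups was approximately 0.3". The formula for the group-by-time interaction is λ = f²·N·m/(1−ρ), with df1 = (k−1)(m−1) and df2 = (N−k)(m−1). Taking ρ = 0.5 and sphericity (both assumed; the article gives neither):

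| Visits m | N needed | Power at N = 44 | Power at N = 56 |
|---|---|---|---|
| 3 | 44 | 0.961 | 0.991 |
| 2 | 52 | 0.904 | 0.965 |

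The stated 44 is reproduced with three visits. This suggests a three-visit model but does not prove one.

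**3. Expected loss**

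44/4 = 11 per group, and 11/(1−0.20) = 13.75, rounded up to 14 per group and 56 in total. This reproduces the plan's figure. The plan thus budgets for losing 56 − 44 = 12 participants. Standard errors with 11 rather than 14 per group are larger by √(14/11) = 1.128, about 13%, but the plan has already allowed for that.

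**4. Possible bias (illustration; every input below is assumed)**

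Suppose there is no true effect and FMA-UE change has SD 1. Suppose participants with the lowest values of a retention score correlated ρ with change are the ones lost. If a proportion p is lost, the mean of those who remain shifts by ρ·φ(z_p)/(1−p), where φ is the standard normal density and z_p the p-quantile.

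- p = 0.10: φ(z)/(1−p) = 0.195
- p = 0.20: 0.350
- p = 0.30: 0.497

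For a comparison of two groups:

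- Equal 20% loss, same mechanism: 0.350ρ − 0.350ρ = 0.
- 10% versus 30%, same mechanism: (0.497 − 0.195)ρ = 0.302ρ, which is 0.09 SD at ρ = 0.3 and 0.15 SD at ρ = 0.5. Against d = 0.6 that is 15% to 25%.
- 20% in both, selective in one group and random in the other: 0.350ρ, which is 0.105 SD at ρ = 0.3 and 0.175 SD at ρ = 0.5.

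**The case against.** A reader might infer that the trial will analyse completers only and report the result as intention-to-treat. The article does not support that as a statement of fact. It nowhere says that withdrawn participants are left out of the analysis, the only principle it states is intention-to-treat, and an imputation rule may stand in the full protocol, the analysis plan or the cited source, none of which is shown. That objection stands.

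Four more limits also stand:

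- Non-collection of T1 and T2 after withdrawal is the natural reading of leaving the trial, but the text is silent rather than explicit.
- Not every missed session counts. Only the stated thresholds trigger withdrawal.
- Lost visits mostly describe data that are already unobtainable, and some who refuse treatment will also decline follow-up. The rule therefore causes only part of the expected loss.
- All groups have the same daily stimulation time, and participants and assessors are to be blinded. This makes a large imbalance in withdrawal less likely, though not impossible. The 10% versus 30% split is an assumption and not a forecast.

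What the objection does not remove is the conflict itself. Withdrawal is a rule on data collection, fixed in the protocol. An analysis plan can choose an imputation method, but it cannot recover outcomes that were not measured, and it cannot turn intention-to-treat into a missing-data method.

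**Conclusion.** The concern holds as a conflict between two statements in the article. Withdrawal from the trial for adherence and clinical events, with no provision for later assessment, does not fit a promise to analyse everyone as randomised. A completer analysis follows only if the standard SPSS repeated-measures procedure is used without imputation. The further loss of people with T0 and T1 but no T2 follows only if all three visits enter that model.

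The direction and size of any bias are unknown. The illustrations run from zero to about 0.15 SD when the selection mechanism is the same in both groups, and to about 0.175 SD when it is not. All rest on assumed loss patterns and correlations. The 13% increase in standard errors is no shortfall against plan, because the enrolment of 56 already covers it. This should be fixed. The documents do not show that the primary analysis is already invalid.

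**What to change.** Leave the criteria on treatment and clinical events as they are and change only what follows for data collection and analysis:

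- State that meeting one of these criteria does not end outcome follow-up. Assess every randomised participant at the scheduled T1 and T2 visits unless consent to follow-up is withdrawn or the participant cannot be reached.
- Treat lost visits as missing data rather than as a withdrawal criterion.
- Analyse all participants by assigned group with a likelihood-based mixed model that uses every observed value. SPSS offers this in its MIXED procedure. The T0 to T1 contrast for the primary outcome can be taken from that model, so a missing T2 costs nobody their T1 value.
- Replace the intention-to-treat sentence with one that names the analysis set and, separately, the method for missing values.
- Label any analysis restricted to adherent participants as per-protocol and supportive.

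A delta-adjusted sensitivity analysis would be a useful option but is not essential to the point.

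The cost is some protocol wording and a few extra assessments at visits already in the schedule. The downside is that some T1 and T2 values will come from participants with incomplete treatment, which is what an intention-to-treat comparison accepts. The possible gain is precision: under the assumptions of the power table, T0 to T1 power is 0.904 with 44 analysed and 0.965 if all 56 are followed. The second figure is an upper limit, since some loss is unavoidable, and it takes the effect as undiluted by incomplete treatment.
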